## Abstract

**Introduction:** Transperineal prostate biopsy is as effective as the transrectal biopsy in detecting prostate cancer and has a lower risk of infection. However, concerning the procedural pain of the transperineal route, a higher level of anaesthesia is needed, which prevents this approach from being widely used. Although several methods of local anaesthesia to relieve pain during transperineal biopsy have been described, few well-designed trials have been conducted to assess the efficacy of local anaesthesia.

**Methods:** This is a prospective, multicentre, randomised controlled study in men suspected of having prostate cancer and planning to undergo transperineal prostate biopsy. The aim of this trial is to determine whether the perineal nerve block and periprostatic block relieve pain to different extents in men undergoing transperineal biopsy. The main inclusion criteria are men aged between 18 and 80 years old, a prostate-specific antigen (PSA) level of 4–20 ng/ml, or/and suspicious rectal examination findings. A sample size of 190 participants, accounting for a 10% loss, is required. All participants will be randomly allocated at a ratio of 1:1 to the perineal nerve block (*n* = 95) and periprostatic block groups (*n* = 95). The primary outcome will be the level of the worst pain experienced during the transperineal prostate biopsy procedure, which will be measured by a numerical rating scale (NRS). The key secondary outcomes will include the pain severity score at 1, 6, and 24 h after prostate biopsy.

**Results:** The primary outcome is the level of the worst pain experienced during the prostate biopsy procedure. The main secondary outcomes are as follows: (1) Post-biopsy pain severity score at 1, 6, and 24 h after the prostate biopsy; (2) Changes in blood pressure, heart rate and breathing rate during the biopsy procedure; (3) External manifestations of pain during biopsy; (4) Anaesthesia satisfaction; (5) The detection rate for clinically significant prostate cancer and any prostate cancer.

**Conclusion:** Anaesthesia in PROstate biopsy Pain Obstruction Study (APROPOS) is randomised controlled trial aiming to determine the efficacy of the perineal nerve block in controlling pain in patients undergoing prostate biopsy *via* the transperineal approach.

**Clinical Trial Registration:**
www.ClinicalTrials.gov, identifier: NCT04501055.

## Introduction

Prostate cancer (PCa) is the second most frequently diagnosed malignancy and the fifth leading cause of death among males worldwide (1). Men with an elevated serum prostate-specific antigen (PSA) level and abnormal findings on digital rectal examinations (DREs) or transrectal ultrasonography (TRUS) examinations are usually suspected of having of prostate cancer. In the clinic, males who are suspected of having PCa typically undergo a prostate biopsy to obtain specimens for pathological diagnosis.

Prostate biopsies are mainly performed by either the transrectal or transperineal approach. Although these two methods differ little in the overall cancer detection rate (2, 3), the transperineal approach has a lower incidence of infection because the instrument is inserted from the perineum to the prostate, which avoiding damage to the rectal wall (4).

While the transperineal approach has merits, the severe pain caused by this approach has prevented its widespread use for prostate biopsies. Compared with the transrectal approach, thetransperineal approach causes more pain (5). Hence, unlike the transrectal approach, which can be performed under local anaesthesia only, transperineal biopsies require general anaesthesia in some cases (6), which takes more time, is costlier, and is associated with more anaesthesia-related risks. To date, several local anaesthesia methods for transperineal biopsy have been described (7–10). The periprostatic block procedure is the recommended and accepted method for patients undergoing a transperineal biopsy (11), although it was first described for use for the transrectal approach (12).

We describe a local anaesthesia method, the perineal nerve block, to reduce the procedural pain of transperineal biopsies; the method was developed on the basis of an anatomical study, and then a single-centre randomizedtrial was conducted to preliminarily verify its efficacy and safety (13). This method showed a reasonable positive effect on pain measured using a visual analogue scale (VAS). Hence, we plan to conduct this multicentre randomised controlled trial to confirm the findings and ensure the results are generalizable.

The aim of this trial is to compare the perineal nerve block and periprostatic block in terms of pain control in patients undergoing a prostate biopsy *via* the transperineal approach. The primary objective is to assess whether the perineal nerve block is superior to the periprostatic block in relieving the procedural pain related to transperineal biopsies.

## Trial Design

In this prospective, multicentre, randomised controlled trial, we anticipate to enrol 190 patients who are scheduled to undergo a transperineal prostate biopsy. The participants will be randomised to the perineal nerve block or periprostatic block groups.

The trial flow chart is shown in Figure 1, and the details and timeframe are shown in Table 1. The primary objective of this study is to assess the efficacy of the perineal nerve block compared with that of the periprostatic block in relieving pain.

**Figure 1 F1:**
[figure not shown]
Trial flow chart.

**Table 1 T1:** Timeline of the study protocol for participants.

**Contact with patient**								
	**Visit 1**	**Visit 2**						**Visit 3**
	**0**	**Pre-biopsy**	**Biopsy procedure**	**1-min post-biopsy**	**1-h post-biopsy**	**6 h post-biopsy**	**24 h post-biopsy**	**2 weeks post-biopsy**
Consent	×							
Screening	×							
Baseline characteristic	×							
PSA	×							
MRI	×							
Randomisation	×							
Perineal nerve block (Perineal nerve block arm)		×						
Periprostatic block (Periprostatic block arm)		×						
Transperineal prostate biopsy (12-core systematic biopsy with/without cognitive targeted biopsy)			×					
Blood presure measurement		×	×	×				
Heart rate measurement		×	×	×				
Breath rate measurement		×	×	×				
External manifestations assessment			×					
NRS pain score assessment				×	×	×	×	
Anaesthesia satisfaction assessment							×	
Pathological assessment								×
Withdrawal	Complete as required at any time following registration							
SAE	Complete as required at any time following registration							

## Outcomes

The primary outcome is the level of the worst pain experienced during the prostate biopsy procedure Pain will be measured by a numerical rating scale (NRS) ranging from 0 to 10, where 0 represents no pain and 10 represents the worst pain imaginable. Additionally, we will measure the pain experienced during the phlebotomizing procedure, with the pain experienced when the needle first touches the skin at the start of anaesthesia as the baseline or reference. Additionally, the adjusted NRS pain score (an adjusted score of 1 will be defined as the worst pain during the biopsy procedure minus the pain of phlebotomizing, and an adjusted of 2 will be defined as the worst pain during the biopsy procedure minus the pain of the needle first touching the skin at the start of anaesthesia) will be reported.

The main secondary outcomes are as follows:
▸ Post-biopsy pain severity score, for which pain will be evaluated by the NRS at 1, 6, and 24 h after the prostate biopsy.▸ Changes in blood pressure, heart rate and breathing rate during the biopsy procedure, which will be measured and recorded by a multi-parameter monitor from 1 min prior to anaesthesia (initial value) to 1 min after the prostate biopsy. The change will be defined as the difference between the average value during the anaesthesia and biopsy procedures and the initial value. Additionally, the difference between the maximum value and the initial value will be assessed.▸ External manifestations of pain during biopsy, which will be assessed by a research nurse who will be blinded to the block arm during the biopsy procedure. The pain assessment will be divided into five parts: the degree of facial expression (0 points for no particular expression or smile; 1 point for an occasional grimace or frown, a withdrawn expression, or a disinterested expression, 2 points for frequent or constant quivering chin or a clenched jaw), the degree of activity (0 points for lying quietly or being in a normal position, 1 point for slight contractions of the hip muscles or slight movements of hip, 2 points for severe contractions of the hip or lifting the hip out of the bed), the degree of voice expression (0 points for quiet or normal communication, 1 point for an occasional moan or weeping sound, 2 points for constant moaning or sobbing and screaming), the degree of pacification (0 points for being peaceful and not requiring pacification, 1 point for being able to be comforted easily, 2 points for being difficult to comfort) and the degree of cooperation (0 points for being calm and cooperative, 1 point for language resistance, 2 points for body resistance).▸ Anaesthesia satisfaction, or patient satisfaction with overall anaesthesia, which will be measured by a questionnaire at 24 h after the biopsy. Five items will be included to evaluate satisfaction: whether the pain during the biopsy was less severe than expected (scores from 0 to 10, where 0 represents far less severe, and 10 represents far more severe than expected); whether the pain after anaesthesia was less severe than the pain during anaesthesia (scores from 0 to 10, where 0 represents far less severe and 10 represent far more severe); weather the patient is satisfied with the overall feeling of the biopsy (scores from 0 to 10, where 0 represents the highest level of satisfaction, and 10 represents the lowest level of satisfaction); whether the patient would recommend this type of biopsy to other patients (scores from 0 to 10, where 0 represents they would highly recommend, and 10 represents they would definitely not recommend it); and whether the patient would still want to choose this way if they have to undergo another biopsy (scores 0 to 10, where 0 represents very willing to choose it and 10 represents extreme reluctance).▸ The detection rate for prostate cancer, defined as the proportion of men with prostate cancer among those who undergo a prostate biopsy.▸ The detection rate for clinically significant prostate cancer, defined as the proportion of men with prostate cancer of International Society of Urological Pathology (ISUP) grade 2 or higher, according to the 2014 ISUP classification, among men who undergo a prostate biopsy.▸ Adverse events, which will be recorded 7 days after this trial. These events mainly include haematuria, vagal reflex, infection, urinary retention and other adverse events identified by the Common Terminology Criteria for Adverse Events (CTCAE).

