## Interventions

### Preparation Before the Block

All participants will be placed in the lithotomy position with a multi-parameter monitor. The participant's blood pressure, heart rate and breathing rate will be measured automatically every min, from 1 min before the anaesthesia procedure to 1 min after the prostate biopsy process. A urologist will be informed of which block method to perform on the spot after the research nurse open a sealed envelope.

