### Perineal Nerve Block Arm

The participants in this arm will undergo a perineal nerve block before a prostate biopsy. The insertion site on the skin will be located on the horizontal line of the anal canal at the upper margin, 20 mm beside the midline. First, the insertion site will be anaesthetized with 10 ml of 1% lidocaine with a 22-gauge 32 mm needle. Then, an advanced injection of perineal nerve block will be carried out with a 20-gauge and 80 mm needle. We will inject 5 ml of 1% lidocaine at each site of the perineal nerve bundle under the guidance of a biplanar ultrasound transducer (Figures 2, 3A).

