### Data Collection and Monitoring

After informed consent is obtained from the patients, the data will be collected by a research nurse who is blinded to the allocation to ensure the integrity of evaluation and prevent bias. Demographic information, including age, body mass index (BMI), PSA level, DRE results, prostate volume and American Society of Anesthesiologists (ASA) classification will be collected before anaesthesia. The pain score will be measured and recorded *via* form 1 (Figure 4) at 10 min, 1, 6, and 24 h after the biopsy. Additionally, the pain of phlebotomizing and the pain at the first moment the needle touches the skin during anaesthesia will be used as the reference and baseline for the pain assessment (form 1). During the biopsy, the external manifestations of pain will be measured *via* form 2 (Figure 5), and the blood pressure, heart rate and breathing rate will be recorded by a multi-parameter monitor. The site of needle core will be reported, because the targeted cores of the anterior zone might be associated with more pain in comparison with those of the peripheric zone (19). Before the participant is dismissed, the anaesthesia satisfaction assessment will be collected *via* form 3 (Figure 6). The pathologic data will be collected within 2 weeks after the biopsy. All of these data will be entered into a particular database. An independent monitor from the APROPOS operation group will check the quality of the data at least twice a week. The monitor may pose queries to the data, and the validity of the data will not be confirmed unless the questions have been resolved.

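### Adjusted score 2 treats as a baseline a pain that arises after the arm is revealed to the operator, and adjusted score 1 subtracts phlebotomy pain where a covariate would be more efficient; the raw-NRS primary outcome is unaffected

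*Protocol article*

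**What the plan says.** The Outcomes section of the protocol article fixes one primary outcome: "The primary outcome is the level of the worst pain experienced during the prostate biopsy procedure", on a 0 to 10 NRS. It then adds two adjusted scores that will be reported as well:

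- Adjusted score 1: "the worst pain during the biopsy procedure minus the pain of phlebotomizing".
- Adjusted score 2: "the worst pain during the biopsy procedure minus the pain of the needle first touching the skin at the start of anaesthesia".

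Data Collection and Monitoring repeats the role given to the second reference, alongside phlebotomy pain: "the pain at the first moment the needle touches the skin during anaesthesia will be used as the reference and baseline for the pain assessment".

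On timing, Randomisation says that the allocation reaches the urologist giving the anaesthesia only once the participant is in the operating room. Preparation Before the Block says: "A urologist will be informed of which block method to perform on the spot after the research nurse open a sealed envelope".

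On the first needle step, the Perineal Nerve Block Arm section says: "First, the insertion site will be anaesthetized with 10 ml of 1% lidocaine with a 22-gauge 32 mm needle". The Periprostatic Block Arm section describes skin anaesthesia with the same drug, concentration, volume and needle. A skin site is given in words for the perineal arm only.

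Statistical Analysis takes the NRS pain score as the dependent variable in a mixed model, with centre as a random effect and imbalanced baseline characteristics as covariates.

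**The concern.** A baseline used for adjustment should be a quantity that the allocated treatment, and knowledge of it, cannot have influenced. First-touch pain does not meet that condition. It is the first event of the anaesthesia procedure and is produced by an operator who has just learned the arm. Subtracting it gives an arm credit for a more painful start, so a difference in score 2 need not reflect analgesia during the biopsy. Because the protocol calls this pain a baseline, it could also be read as eligible for the covariate slot that the primary model reserves for imbalanced baseline characteristics. That is a possible reading, not a stated plan.

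Phlebotomy pain is a different case. The block does not produce it, so score 1 does not carry this bias. The issue there is efficiency: subtraction fixes the adjustment slope at 1 whatever the true relation between the two pains, while a covariate lets the data estimate the slope.

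**Working it through.** **Inputs from Sample Size:** means 2.0 and 2.5 (difference 0.5), SD 1.0 in each arm, two-sided α 5%, power 90%, 1:1 allocation, 86 per arm.

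**Assumed, because the document does not give them:** the correlation ρ between biopsy pain and the reference pain, the SD of the reference pain (sX), and the arm difference b in first-touch pain.

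**Step 1. The plan's own figure.** The normal approximation gives n = 2(1.960 + 1.282)² × 1.0² / 0.5² = 84.1, so 85 per arm. The t-test solution is 85.03, which rounds up to 86. The stated 86 per arm reproduces, and it rests on the raw NRS. Power at 86 per arm is 90.3%.

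**Step 2. Score 2, shift of the contrast.** Write each contrast as periprostatic minus perineal. Then

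adjusted contrast = raw contrast − arm difference in first-touch pain.

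| Assumed first-touch pain | Adjusted contrast if the raw contrast is 0.5 |
|---|---|
| equal in both arms | 0.5 |
| 0.25 higher in the perineal arm | 0.5 + 0.25 = 0.75 |
| 0.25 higher in the periprostatic arm | 0.5 − 0.25 = 0.25 |
| 0.5 higher in the perineal arm | 0.5 + 0.5 = 1.0 |
| 0.5 higher in the periprostatic arm | 0.5 − 0.5 = 0 |

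The arm with the more painful first contact gains in every case. The direction follows from the definition; the size of b is an assumption.

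**Step 3. Score 1, subtraction against covariate.** With biopsy-pain SD sY:

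- Var(subtraction) = sY² + sX² − 2ρ·sX·sY, which is 2(1 − ρ) when both SDs are 1.0.
- Var(covariate) = sY²(1 − ρ²), which is 1 − ρ² when sY = 1.0.
- Their difference is (sX − ρ·sY)², which is never negative. The covariate is therefore never less precise, apart from the one degree of freedom spent on the slope out of 170.

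t-test power for a difference of 0.5 at 86 per arm, both SDs 1.0, ignoring centre:

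| ρ (assumed) | SD, subtraction | Power | SD, covariate | Power |
|---|---|---|---|---|
| 0.2 | 1.26 | 73% | 0.98 | 91% |
| 0.3 | 1.18 | 79% | 0.95 | 93% |
| 0.5 | 1.00 | 90% | 0.87 | 96% |
| 0.6 | 0.89 | 95% | 0.80 | 98% |
| 0.7 | 0.77 | 99% | 0.71 | >99% |

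**Step 4. When subtraction loses against the raw score.** Var(subtraction) exceeds sY² when sX² > 2ρ·sX·sY, that is when ρ < sX/(2sY). With sY = 1.0 the threshold is 0.25 for sX = 0.5, 0.5 for sX = 1.0 and 0.75 for sX = 1.5. Above the threshold, subtraction is more precise than the raw score, though still no better than the covariate.

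**The case against.** The strongest reply is that the adjusted scores are supplementary. The protocol names one primary outcome, powers on it and models it, and nothing says that either adjusted score is tested or supports the superiority conclusion. That stands, and it limits the point to how these scores are built and labelled.

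A reader might also infer three stronger things that the documents do not support.

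- **That score 2 rewards the arm with the more painful block injection.** It does not. The subtracted pain is the first skin contact, and that step uses the same drug, concentration, volume and needle in both arms; the longer block needle comes later. The skin site missing from the periprostatic text does not show that the sites differ, since the figure is not available here and an article may leave the site to the full protocol. No arm difference in first-touch pain is shown.
- **That subtraction will cost precision against the raw score.** That depends on a correlation and an SD that the document does not give, and it reverses above the threshold in step 4.
- **That scoring first-touch pain breaks the nurse's blinding.** The document does not say when or by whom that pain is scored; the patient could report it afterwards.

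What remains after these replies is the mislabelled baseline, the one-for-one passage of any arm difference into score 2, and the inefficiency of subtraction relative to a covariate.

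**Conclusion.** The point holds in a limited form. First-touch pain is not a baseline, because it arises after the operator learns the arm. Score 2 therefore cannot be read as a baseline-adjusted treatment effect. If the first-touch pains differ by b, the score is off by exactly b, and against a planned effect of 0.5 even an assumed 0.25 halves it or raises it by half. Whether b differs from zero is unknown.

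Score 1 is not biased by the block, but it uses a helpful measurement in the less efficient way. At equal SDs and assumed correlations of 0.2 to 0.5, subtraction gives about 73% to 90% power, against 91% to 96% with the covariate. The power figures are illustrations, because the trial is not powered on the adjusted scores.

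It would be wrong to conclude that the main result is compromised: the raw-NRS primary outcome and the 86 per arm are unaffected.

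**What to change.** 1. In Outcomes and Statistical Analysis, replace adjusted score 1 by entering phlebotomy NRS as a prespecified covariate in the primary mixed model, whether or not it turns out to be imbalanced.
2. State that phlebotomy pain is scored before the envelope is opened. The article does not fix this: the NRS row in Table 1 starts only after the biopsy, and a score recalled then could be coloured by the block and the biopsy.
3. In Outcomes and in Data Collection and Monitoring, stop describing first-touch pain as a baseline. State that it will not be a covariate and that adjusted score 2 will not serve as evidence of efficacy.
4. Report first-touch pain by arm, descriptively.

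The cost is small: wording in three sections and a fixed scoring time for one existing form item. No new data are needed. Who records the scores can stay as the Blinding section has it.

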### Sample Size

The prospective data in our previous study showed a mean maximal VAS score of 1.8 for patients who underwent a biopsy with a perineal nerve block and a mean maximal VAS score of 3.4 for those who received a periprostatic block. The standard eviations for these two methods were 1.02 and 0.96, respectively.

For the calculation of sample size, using a power of 90%, a two-sided α of 5%, and an allocation ratio of 1:1 and assuming an NRS score for the perineal nerve block of 2.0, an NRS score for the periprostatic block of 2.5, and the standard deviations for these two methods are equal to 1.0, 86 men per arm will be required. Accounting for a withdrawal/loss rate of 10%, a total of 190 participants are required for inclusion.

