### Statistical Analysis

The primary outcome in this trial will be analysed following the intention-to-treat principle as well as the per-protocol principle. The difference between the two groups will be evaluated with a 95% confidence interval (CI) using a generalised linear mixed model to express the precision of the estimate. In this model, the NRS pain score and the group will be considered the dependent variable, the imbalanced baseline characteristic will be considered the covariate, and the centre will be considered a random effect.

The secondary outcomes will be analysed with Pearson chi-square tests and expressed with 95% CIs. Each *P*-value reported in this trial will be two-sided.

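### The vital-sign outcomes use the initial value only by subtraction; adjusting for it as a covariate would cost nothing and could sharpen these secondary comparisons

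*Protocol article*

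**What the plan says.** The Outcomes section of the protocol article lists changes in blood pressure, heart rate and breathing rate among the main secondary outcomes, recorded "from 1 min prior to anaesthesia (initial value) to 1 min after the prostate biopsy". It defines the outcome in two ways:

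- Average: "The change will be defined as the difference between the average value during the anaesthesia and biopsy procedures and the initial value".
- Maximum: "Additionally, the difference between the maximum value and the initial value will be assessed".

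Preparation Before the Block adds that these signs "will be measured automatically every min, from 1 min before the anaesthesia procedure to 1 min after the prostate biopsy process". The procedure average therefore pools several readings, while the initial value rests on about one.

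The Statistical Analysis section says of all secondary outcomes: "The secondary outcomes will be analysed with Pearson chi-square tests and expressed with 95% CIs". A covariate rule appears only for the model of the NRS pain score, where "the imbalanced baseline characteristic will be considered the covariate, and the centre will be considered a random effect". The pre-anaesthesia demographic items listed under Data Collection and Monitoring (age, BMI, PSA, DRE, prostate volume, ASA class) do not include vital signs. The article nowhere uses the initial vital sign as a covariate, and nowhere forbids it.

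**The concern.** Comparing mean changes between arms without adjustment is the same as fixing the slope of the procedure value on the initial value at 1. If the true slope is lower, because a man who is high just before the procedure tends to drift back whatever the block, subtraction over-corrects. The arm that happens to start lower then tends to show the larger rise. Across randomisations this appears as extra variance in the estimated arm difference.

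What is at stake is precision in a set of secondary outcomes. The Discussion says the monitor readings will be considered alongside the subjective NRS scores to broaden the assessment of pain control. Wider intervals than the data allow make a real difference in these signs easier to miss.

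**Working it through.** **The plan's own figure.** The only sample size stated is for the primary NRS outcome, "using a power of 90%, a two-sided α of 5%, and an allocation ratio of 1:1", with means of 2.0 and 2.5 and SD 1.0. The normal formula, 2(1.960 + 1.282)²/0.5², gives 84.1, so 85 per arm. The t-test version gives 85.03, so 86, as stated. The total follows from 172 × 1.10 = 189.2, so 190. I use 86 per arm below. The plan gives no figure for the vital signs.

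**Inputs not in the documents.** The SD of the initial value (sx), the SD of the procedure value (sy) and their correlation (ρ) are assumptions, so a range is shown.

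**Formulas, per man.**
- Unadjusted change: sx² + sy² − 2ρ·sx·sy
- Adjusted for the initial value: sy²(1 − ρ²)
- Difference between the two: (sx − ρ·sy)²

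The difference is never negative. It is zero only when sx = ρ·sy, that is, when the slope ρ·sy/sx equals 1. With equal SDs the variances are 2(1 − ρ) and 1 − ρ², in units of the common variance, and their ratio is (1 + ρ)/2.

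**Power.** Take an effect with 80% power under adjustment (two-sided 5%, 86 per arm). Power with raw change is Φ(2.802 × √ratio − 1.960). At ρ = 0.5 this is Φ(2.802 × 0.866 − 1.960) = Φ(0.466) = 0.68.

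| ρ (assumed) | Raw variance | Adjusted variance | Adjusted/raw | Power with raw change |
|---|---|---|---|---|
| 0.3 | 1.40 | 0.91 | 0.65 | 62% |
| 0.5 | 1.00 | 0.75 | 0.75 | 68% |
| 0.7 | 0.60 | 0.51 | 0.85 | 73% |
| 0.9 | 0.20 | 0.19 | 0.95 | 78% |

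**Closer to the measurement scheme.** Suppose the average of 10 readings (an assumed number) is set against one initial reading, with every pair of readings equally correlated at r. The slope of the average on the initial reading is then r. At r = 0.5, 0.7 and 0.9 the variance ratio is 0.55, 0.73 and 0.91, and power with raw change is 54%, 67% and 76%. The maximum may have a different slope.

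**Where the lost precision comes from.** For the estimated arm difference, Var(raw) = Var(adjusted) + (1 − slope)² × Var(baseline difference). With equal SDs, ρ = 0.5 and 86 per arm, in squared SD units, Var(baseline difference) = 2/86 = 0.0233. So 0.0233 = 0.0174 + 0.25 × 0.0233. Chance baseline imbalance accounts for all of the extra variance.

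**Simulation** (20,000 trials, ρ = 0.5, 86 per arm).
- The SE of the arm difference was 0.152 SD with raw change and 0.132 SD with adjustment, a variance ratio of 0.755.
- Both estimates averaged about zero when there was no effect.
- The raw-change estimate moved by −0.50 per unit of chance baseline difference; the adjusted estimate moved by about zero.
- Adjusting the change for the initial value, or adjusting the procedure value itself, gave the same arm difference (largest discrepancy 3 × 10⁻¹⁶).

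**The case against.** The strongest objection is that the Outcomes section only defines a variable. A reader might infer that defining the outcome as a change is itself what loses precision. The documents do not support that: a change score modelled with the initial value as covariate gives the same arm estimate as the adjusted procedure value. The loss arises only when the definition is combined with the covariate-free test in the Statistical Analysis section. This part of the objection stands, and the remedy belongs in that section.

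A reader might also infer that the vital-sign comparison is biased. It is not. Averaged over randomisations, raw change is unbiased and its interval has nominal coverage. The shift is conditional on the imbalance that happens to arise. It is the same effect as the lost precision and should not be counted as a second harm.

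The power figures compare two analyses of a continuous change, and the article states neither. It names a Pearson chi-square test, which does not suit a continuous change unless the change is categorised. That mismatch is a separate and more serious matter. Replacing the test with a t-test on the changes would still leave the present point open.

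Finally, a condensed article may leave covariates to an analysis plan that is not shown. That plan could add the adjustment. But the article is not silent here: it states both the outcome and its test, and the only baseline handling it states is subtraction.

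**Conclusion.** The point holds as a minor, efficiency-only improvement to secondary outcomes. As stated, the initial vital sign enters only by subtraction. In large samples an unadjusted comparison of changes cannot be more precise than an adjusted one, apart from one degree of freedom, and it is less precise whenever the slope is not 1.

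The size is uncertain because the documents give no SD or correlation. With equal SDs, the loss runs from substantial (variance ratio 0.65, power 62% against 80%) at a correlation of 0.3 to nearly nothing (0.95, 78%) at 0.9. Readings taken minutes apart on the same man could well be highly correlated, so a large loss should not be presumed. The primary NRS comparison and the sample size are unaffected.

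**What to change.** Keep both change definitions in the Outcomes section as descriptive measures. In the Statistical Analysis section, state that the procedure average and, separately, the maximum of each vital sign (or their changes, which give the same arm difference) will be compared between arms with a linear mixed model. The model should have arm and the man's initial value of that sign as fixed terms, the initial value being prespecified whether or not the arms look imbalanced, and centre as a random effect, as in the primary model. Report the adjusted mean difference with its 95% CI.

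The cost is one sentence and one degree of freedom per model. The initial value is already recorded before the block, so no extra men or measurements are needed. Fixing the covariate in advance also removes any choice about adjustment after the results are seen.
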